#### Biomechanics

Eight Motion Analysis cameras (Motion Analysis Corp., Santa Rosa, CA) sampling at 240 Hz will record the 3D trajectories of retroreflective markers placed over the participants most symptomatic limb as they walk along a 20 m runway. A force platform (Kistler AG, Winterthur, Switzerland) will collect ground reaction force data at a frequency of 2400 Hz as the participant walks along the runway. This will be done for 5 successful trials in each of 3 footwear conditions for each participant: (1) participant’s own shoe (baseline condition), (2) participant’s own shoe with the lateral wedge insole, and (3) participant’s own shoe with the medial wedge insole. A successful trial is defined as one where the participant lands with their most symptomatic limb near the center of the force platform, does not touch the force platform with their other limb, and maintains a gait speed of 1.3 ± 0.07 m/s as measured by two photocells.

Kinetic and kinematic data will be filtered using 4^th^ order Butterworth low-pass filters with cut-off frequencies of 50 Hz and 12 Hz, respectively. KAMs during stance will be calculated using an inverse dynamics approach, and the peak KAM (first peak) will be identified for each trial [4, 19]. The average KAM across trials for each footwear condition will then be calculated and represented as a percent change from the baseline condition value. The KAM impulse (integral of KAMs with respect to time) and Varus thrust (maximum mediolateral displacement of knee joint center from touchdown) [24] and the KAM impulse (integral of KAMs with respect to time) [25] will also be calculated as these variables have also been shown to be related to knee OA [6, 24]. At the baseline visit, biomechanical testing and DXA scans will be performed and survey information will be collected. After determining the peak KAMs for all three conditions, the percent change in KAM will be determined for the medial and lateral wedge conditions.

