### Randomization

Following the baseline laboratory and survey testing, participants will be randomized into one of two study arms: (1) a KAM-reduction experimental group (KAM-R), or (2) a waitlist control group. In the KAM-R group, participants will be given either a medial or lateral wedge insole (whichever insole reduces KAMs more for each individual participant) to put inside their own shoe and use for 3 months. In the waitlist control group, participants will be asked to continue using their own shoes for a period of 3 months, and following this will be provided with access to a wedged insole (whichever reduces KAMs more based on baseline data collection).

Participants will be randomized using a multi-block-randomization procedure into either the KAM-R or waitlist control group. Specifically, a separate block sequence will be used for males and females to ensure an even sex distribution across groups. A block size of 6 will be used for each, and the sequence will be determined from a random number generator.

The one exception to this block randomization procedure is that if neither wedged insole produces a KAM reduction, the participant will be excluded from the main study altogether. This scenario will not be common, as most people do experience a large change in KAMs with one of the two wedged insole types, but this strategy will ensure that all participants in the KAM-R and waitlist control groups are all biomechanically suitable for a wedged insole intervention. Thus, neither group will contain biomechanical non-responders to wedged insoles.

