#### Within group analyses

All data will be analyzed on an intention to treat basis. Changes from baseline to 3 months will be assessed within groups for ordinal data (UCLA score) using Wilcoxon Signed Rank test (α = 0.05). KOOS subsection scores and PASE scores will be compared between baseline and at 3 months using paired-samples t-tests (α = 0.05). KAMs, KAM impulse, varus thrust, and footwear comfort will be compared between the neutral shoe and assigned wedged insole condition at baseline for the KAM-R group using paired-samples t-tests (α = 0.05). All tests will be two-tailed, except in the case of KAMs and KAM impulse, where one-tailed tests will be used. The reason for this is that KAM reduction is strictly controlled in this study and so KAM and KAM impulse reductions are the only possible outcome.

A multivariable linear regression (α = 0.05) will also be conducted on the KAM-R group to evaluate whether KAM reduction, KAM impulse, varus thrust and footwear comfort can predict change in pain over 3 months. Covariates tested in these four models will include adiposity and Kellgren-Lawrence grade.

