## Discussion

The primary goal of this randomized controlled trial is to identify the influence of reduced KAMs on management of knee OA symptoms. In this study, wedged footwear insoles will be used as the intervention to induce reduced KAMs. Wedged insoles are a relatively inexpensive and easy-to-use intervention, and have been a recommended management strategy in numerous international clinical guidelines for OA. However, some randomized trials conducted on wedged insoles have shown inconsistent results. The primary reason for this is that previous studies used exclusively a lateral wedge insole and did not test each participant’s biomechanics to ensure that the lateral wedge actually reduced KAMs. Indeed, it has been found in numerous studies that lateral wedges may in fact increase KAMs during gait for some participants, which could induce OA worsening, and wash out any actual treatment effects of reduced KAMs that may be observed in other participants [12, 13]. Thus, in our study, we are testing both medial and lateral wedge insoles, and prescribing the insole that reduces KAMs the most. This will ensure that all participants in our KAM-R group experience reduced KAMs.

Another reason why other wedged insole studies have shown mixed results on OA management is that these studies used inadequate control interventions. Specifically, some studies have given all control participants a flat neutral insole. Other studies have provided a new shoe to all participants as a control condition [40]. While in theory this is appropriate as an attempt to protect against placebo effects and provided a method for blinding, it does carry the possibility that some participants will experience altered KAMs during gait. For instance, McCormick et al. [23] have shown that control insoles alter pressure distributions relative to a no insole condition, and this pressure shift could affect KAM magnitude [4]. Therefore, in our study, we have chosen to utilize the participant’s own shoe as a control condition to ensure biomechanics remain unchanged. Our regression analyses will provide some insight into whether placebo effects do exist with wedged insoles. For instance, if the slope of the line of best fit is not near zero, it would suggest that change is pain is related to a reduction in KAM regardless of whether a placebo effect exists or not.

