## Conclusions

In conclusion, this will be the first study to isolate the effects of reduced KAMs on symptom management for patients with mild to moderate medial knee OA over a follow-up period of 3 months. This study could therefore have strong clinical implications regarding personalized prescription of wedged insoles.

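### The KAM-R-only regression of pain change on KAM reduction is open to prognostic confounding and cannot show whether a placebo effect exists; a both-arm model from data already collected would help

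*Protocol article*

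**What the plan says.** Under Within group analyses, a multivariable linear regression "will also be conducted on the KAM-R group to evaluate whether KAM reduction, KAM impulse, varus thrust and footwear comfort can predict change in pain"; the change is taken from baseline to the 3-month visit. On adjustment, the same section says: "Covariates tested in these four models will include adiposity and Kellgren-Lawrence grade". Baseline KOOS pain is not named.

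The predictor is also recorded in the controls. On gait testing, the Biomechanics section says: "This will be done for 5 successful trials in each of 3 footwear conditions for each participant". The conditions are own shoe, lateral wedge and medial wedge. Under Randomization, each control's later insole is "whichever reduces KAMs more based on baseline data collection". Participants whose KAM falls with neither wedge are excluded from both arms: "Thus, neither group will contain biomechanical non-responders to wedged insoles".

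The Discussion says that the regressions will give some insight into whether placebo effects exist, and that "if the slope of the line of best fit is not near zero, it would suggest that change is pain is related" to KAM reduction whether or not there is a placebo effect. The Conclusions say that "this will be the first study to isolate the effects of reduced KAMs on symptom management".

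**The concern.** Randomisation decides who gets an insole. It does not decide how far a given person's KAM falls with it. Within the KAM-R arm, the size of that fall is a patient characteristic, and it may go along with baseline pain, alignment or gait. Any of these may predict 3-month pain change without an insole effect. Baseline pain deserves particular attention: the outcome is a change score, and entry requires a KOOS pain score of 75 or lower, so some regression to the mean is to be expected.

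The regression carries weight. The control is an unblinded waitlist without placebo, between-group comparisons are labelled exploratory, and the Discussion offers the slope as its answer on placebo. A slope that reflects prognosis could be read as support for the load-reduction hypothesis.

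**Working it through.** **The plan's own figure.** Inputs from Sample size calculation: difference 13.4, SD 15, two-sided 0.05, power 80%. The two-sample formula gives 2 × (15/13.4)² × (1.96 + 0.84)² ≈ 19.7, so 20 per group, and 40 × 1.15 = 46. A paired formula with zero correlation between baseline and 3 months also gives 20. The stated figures therefore reproduce. No power is stated for the regression. With 20 evaluable KAM-R participants, the smallest correlation detectable with 80% power is tanh(2.80/√17) = 0.59; with 23 it is 0.56.

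**How a slope arises without a KAM effect.** Let r be the correlation of KOOS pain between baseline and 3 months, and c the correlation of baseline KOOS pain with KAM reduction. Through baseline pain alone, the slope of change per SD of KAM reduction is −(1 − r) × 15 × c:
- r = 0.5, c = −0.3: 0.5 × 15 × 0.3 = 2.25 points
- r = 0.5, c = −0.5: 0.5 × 15 × 0.5 = 3.75 points
- r = 0, c = −0.5: 1 × 15 × 0.5 = 7.5 points

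The documents give neither r nor c. These values are assumptions.

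**Simulation with the planned covariates** (20 per arm, SD 15, 4,000 runs, no true KAM effect). Entries are mean slope in KOOS points per SD of KAM reduction, with the rejection rate in brackets.

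| Assumed scenario | KAM-R only, as planned | KAM-R only plus baseline pain | Both arms, arm-by-response interaction |
|---|---|---|---|
| c = −0.3, r = 0.5 | 2.3 (9%) | 0.05 (5%) | 0.1 (5%) |
| c = −0.5, r = 0.5 | 3.8 (18%) | 0.1 (5%) | 0.1 (5%) |
| c = −0.5, r = 0 | 7.3 (30%) | 0.0 (5%) | −0.4 (5%) |
| Prognosis by another route, 5 points per SD | 5.0 (24%) | 5.0 (30%) | 0.1 (5%) |
| Placebo effect of 10 points, equal for all | 0.0 (5%) | 0.0 (5%) | 0.0 (5%) |
| Placebo response growing by 5 points per SD | 5.1 (25%) | 5.0 (30%) | 5.1 (16%) |

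Baseline pain removes only what runs through baseline pain. The interaction removes both prognostic routes. Neither removes a placebo response that grows with KAM response.

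**Simpler illustration, no covariates.** If KAM response correlates 0.15, 0.3 or 0.4 with natural pain change, the one-arm slope at n=20 is significant in about 9%, 25% or 43% of trials. The interaction stays near 5%.

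**Price of the interaction.** It is a difference of two independent slopes from arms of equal size, so its standard error is about √2 ≈ 1.4 times that of one slope. For a true effect of 5 points per SD, power is about 25% for the planned slope, 16% for the interaction, and 19% for the interaction with baseline pain.

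**The case against.** Several points on the other side stand.

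- The Discussion is hedged: it speaks of some insight and of a relation. A reader might infer that it claims pain change is caused by KAM reduction, or that the slope is separated from prognosis. It says neither. The unhedged wording is in the Conclusions, and it describes the study as a whole.
- A reader might infer that any placebo effect biases the slope. It does not. An effect equal for all participants goes into the intercept, and there the Discussion is right.
- The covariate sentence need not be exhaustive, this is a condensed article, and Kellgren-Lawrence grade already covers part of severity. Omitting baseline pain biases the slope only if baseline pain is associated with KAM response, which is unknown.
- The control KAM data are not idle: they serve for exclusion, for the choice of the later insole and for baseline comparison. They are only absent from this regression.
- A reader might take the both-arm interaction as proof of mechanism. Controls receive no insole and KAM response is not randomised, so a placebo response or another effect modifier that varies with KAM response would remain.

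What does not stand is that hedging or the covariate list rescues the inference. The one-arm restriction and the reading of the slope are both fixed in the text, and prognosis by a route other than baseline pain passes straight through the planned model.

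**Conclusion.** The point holds in limited form. In one arm, a non-zero slope on a non-randomised KAM response does not distinguish a KAM effect from prognosis. Because a uniform placebo effect leaves the slope unchanged, the slope cannot show whether such an effect exists. The randomised contrast compares a KAM-selected insole, placebo included, with a waitlist, so it does not isolate the effects of reduced KAMs either.

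In the prognostic scenarios with the planned covariates, false-positive rates are 9% to 30% against a nominal 5%. These figures, like the 9%, 25% and 43% above, rest on assumed associations. They show what could happen and do not predict the trial's error rate; with no such association the planned slope keeps its 5%. This is a secondary analysis, and the remedy is a cheap improvement to it.

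**What to change.** 1. Keep the planned KAM-R models and add baseline KOOS pain to each.
2. Add an exploratory both-arm model for each predictor measured at baseline in both arms: KAM reduction, KAM impulse, varus thrust, and comfort if it was recorded for each insole. Use the value with the assigned insole or, for controls, with the insole that they would have received. Terms: arm, that predictor, their interaction and baseline KOOS pain. Report the control-arm slope as the prognostic check.
3. State that the interaction removes prognostic confounding but not a placebo response or other effect modification that varies with KAM response, so it does not by itself prove mechanism.
4. Soften the Discussion and Conclusions. The randomised comparison estimates a KAM-selected insole versus waitlist, including placebo. Drop the claim to isolate KAM effects and the suggestion that the slope shows whether placebo effects exist.

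Cost: analysis wording and data already collected; no new visits or participants. The price is precision, as worked out above, so results should be given as estimates with confidence intervals and labelled exploratory.

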Across 13 international clinical guidelines for management of knee OA, wedged insoles (i.e. insoles that elevate either the lateral or medial aspect of the foot) have been consistently recommended for disease management since they can influence KAMs [10]. On average across patients, laterally wedged insoles have been shown to reduce KAMs and reduce pain, while medially wedged insoles tend to increase KAMs; [4, 11] however, when considering subject specific reactions, 15-43% of patients, depending on the study, receiving either a medial or lateral wedge will experience KAM changes that are completely opposite to the group average result [12, 13]. This means that every year, thousands of North Americans with knee OA are being prescribed an incorrect wedge resulting in increased KAMs, and possibly accelerating and worsening their OA.

Interestingly, when reviewing past literature of major randomized trials for knee OA, no study has actually ensured that all patients experienced a reduction in KAMs in the experimental insole group, and this has likely had a large bias on study results [14, 15]. Thus, it is no surprise that a recent review has highlighted that large variability exists across studies in terms of the effectiveness of lateral wedge insoles [16]. Essentially, we still do not truly understand how or if wedged insoles and reduced KAMs can benefit patients with knee OA. Therefore a randomized trial is urgently needed that assigns wedged insoles on a personalized basis to ensure that KAMs are being reduced. Thus, the primary purpose of this study is to evaluate the effectiveness of a personalized wedged insole intervention on pain in patients with medial knee OA. Specifically, KAMs must be measured for each participant to ensure KAM reduction occurs with the intervention insole, rather than providing all patients with the exact same insole and assume a constant KAM effect as previous trials have done. This approach of ensuring KAM reduction has never been attempted before and so the results from this study will help evaluate the true clinical benefit of KAM reduction, and also the true effectiveness of wedged insoles. It is hypothesized that patients in the experimental group, where KAMs have been reduced using an individually prescribed wedged insole, will overall have greater improvements in pain and physical function over 3 months compared to the control group.

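### The KAM-R pain regression pools lateral- and medial-wedge wearers without a wedge-type term, so part of a non-zero KAM slope could be a wedge-type difference

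*Protocol article*

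**What the plan says.** - **Assignment.** Under Randomization, in the KAM-R group "participants will be given either a medial or lateral wedge insole (whichever insole reduces KAMs more for each individual participant"). Wedge type is therefore not randomised. It follows from the same baseline gait measurement that supplies the KAM-reduction predictor.
- **Model.** Under Within group analyses, a regression in the KAM-R group alone is to "evaluate whether KAM reduction, KAM impulse, varus thrust and footwear comfort can predict change in pain over 3 months". The covariates follow: "Covariates tested in these four models will include adiposity and Kellgren-Lawrence grade". The reference to four models suggests one per predictor, so footwear comfort would not be in the KAM model.
- **Wedge type elsewhere.** Neither Within group analyses nor Between group analyses uses wedge type as covariate, stratum, subgroup or descriptive factor.
- **Reading rule.** The Discussion says of a slope not near zero that "it would suggest that change is pain is related to a reduction in KAM regardless of whether a placebo effect exists or not".
- **Background on the wedges.** On average, "laterally wedged insoles have been shown to reduce KAMs and reduce pain, while medially wedged insoles tend to increase KAMs". However, "15-43% of patients, depending on the study, receiving either a medial or lateral wedge will experience KAM changes that are completely opposite", the reference being the average response in the study concerned.

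**The concern.** The KAM-R arm contains two devices that tilt the foot in opposite directions, worn by two kinds of patient sorted by their gait response. If one group has larger KAM reductions and also a different pain course for reasons unrelated to KAM (the device itself, comfort, the type of patient), a pooled slope mixes two things: the relation of pain to KAM reduction among people wearing the same wedge, and the difference between the two wedge groups. Only the first is what the Discussion wants to read from it.

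The control arm has no placebo insole and participants know their allocation. These regressions are the only planned link between pain change and the size of the load reduction, and the Discussion relies on them to answer the placebo question. A slope partly due to wedge type would be reported as a relation with KAM reduction.

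**Working it through.** **Inputs from the protocol.** SD 15 points, target change 13.4 points and 20 per group (Sample size calculation); two-sided α = 0.05 (Within group analyses). The 20 reproduces as 2(1.960 + 0.842)² × 15² / 13.4² = 19.67, rounded up. The protocol gives no figure for the regression itself.

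**Assumptions, not in the documents.**
- p, the share on the medial wedge: 15-43%. This borrows the Background range for opposite responders, which is not the same quantity. It means about 3 to 9 of 20.
- δ, the shortfall in mean KAM reduction among medial wearers.
- γ, the shortfall in their pain improvement by routes other than KAM.
- SD of KAM reduction within wedge type: 4 percentage points. Residual SD of pain change: 15. True effect of KAM reduction within wedge type: zero.

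**Formulas**, with q = p(1 − p) and 4² = 16:
- spurious slope = γδq / (16 + δ²q), in KOOS points per 1% KAM;
- weight of the between-wedge contrast in the pooled slope = δ²q / (16 + δ²q);
- SE ratio after adding wedge type, from collinearity = √[(16 + δ²q) / 16].

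| Setting | p | δ | γ | δ²q | Spurious slope | Between-wedge weight | SE ratio |
|---|---|---|---|---|---|---|---|
| mild | 0.15 | 3 | 5 | 1.15 | 1.91/17.15 = 0.11 | 7% | 1.04 |
| middle | 0.30 | 4 | 10 | 3.36 | 8.40/19.36 = 0.43 | 17% | 1.10 |
| extreme | 0.43 | 6 | 13.4 | 8.82 | 19.71/24.82 = 0.79 | 36% | 1.25 |

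Simulating pain change on KAM reduction with n = 20 gives false-positive rates of about 5%, 8% and 16-17% in these three settings. With wedge type added, all return to about 5%.

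**Second simulation, closer to the planned model.** Adiposity and Kellgren-Lawrence grade are included, with 20,000 runs per setting. The KAM gap d is in within-type SDs (δ = 4 above is d = 1). The ranges run over p = 0.15, 0.30 and 0.43, with n = 20.

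| d | γ | False positives, as planned | With wedge type |
|---|---|---|---|
| 0 (any γ), or any d with γ = 0 | – | about 5% | about 5% |
| 1 | 6.7 | 5.4-6.5% | about 5% |
| 2 | 6.7 | 6.4-9.6% | about 5% |
| 1 | 13.4 | 7.0-11.4% | about 5% |
| 2 | 13.4 | 11.2-22.0% | about 5% |

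Both gaps must be present for any inflation, and both must be large for it to be substantial.

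**Is a KAM gap to be expected?** Suppose, for illustration, that each person's medial response is the exact negative of their lateral response, the lateral response is normal, and the better wedge is worn. Medial wearers then have smaller mean reductions by about 1.0, 0.6 and 0.2 within-type SDs at medial shares of 15%, 30% and 43%. Some gap follows from the assignment rule, but it shrinks as the medial share grows. The large-share, large-gap combination behind the highest rates is therefore not what this simple model predicts. Under it, false positives are about 5-7%.

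**The case against.** **Two gaps are needed and neither is documented.** The opposite average effects in the Background describe unselected patients. Here everyone wears the wedge that reduces KAM more, and those with no reduction are excluded. No passage reports a pain difference between wedges by a non-KAM route, and Footwear insole interventions treats the wedge purely as a vehicle for the mechanical change. This stands as a limit on size. It does not remove the point, because no planned analysis checks that premise.

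**The covariate list may not be closed.** The verb used is include, and this is a condensed article without its analysis plan. That is fair for covariates in general. However, the article fixes the model's named covariates and also how its slope will be read, and that pairing is what needs the qualification.

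**The Discussion is cautious.** It promises some insight and uses associational wording. That is so, but the sentence allows for placebo effects and not for wedge type.

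**Tempting stronger readings.** A reader might infer that the slope is simply a lateral-versus-medial contrast. The arithmetic does not support this: in the three worked settings 64-93% of its weight is within wedge type. A reader might also infer that medial wearers benefit less, or that the trial's pain results are compromised. The documents show neither.

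**Splitting the treatment effect by best wedge would not help much.** With 3 against 3 participants, the 95% half-width is 2.776 × 15 × √(2/3) = 34 points. With 9 against 9 it is 2.120 × 15 × √(2/9) = 15 points. Both exceed 13.4, so this contrast is not proposed as a remedy.

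**Conclusion.** The point holds in a conditional form. The plan pools two non-randomly assigned wedges, names no wedge-type term, and attaches to the slope a reading that pooling can undermine. If the wedge types differ both in mean KAM reduction and in pain change outside KAM, part of the slope is a wedge-type contrast.

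Under assumed gaps, with n = 20 and no true load effect, the false-positive rate is about 5-8% in mild to middle settings, up to about 11% in intermediate ones where one of the gaps is large, and about 16-22% only in extreme ones. If either gap is absent it stays at 5%. The medial share, both gaps and the SD of KAM reduction are assumptions throughout.

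This concerns a secondary, non-randomised analysis. The KOOS pain comparisons within and between groups do not depend on it. It is a cheap improvement, not an error that threatens the trial.

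**What to change.** 1. In Within group analyses, state that each pain-prediction slope will be reported with and without wedge type (lateral/medial) as a covariate, with confidence intervals.
2. In the Discussion, read a non-zero slope as related to KAM reduction only if it persists after that adjustment.
3. Tabulate, descriptively for the KAM-R group, the number on each wedge and the KAM reduction and pain change by wedge type.

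No new data are needed, since wedge type is known for every KAM-R participant. The adjusted model loses one degree of freedom: with 20 participants and four fitted terms (intercept, KAM reduction, adiposity, Kellgren-Lawrence grade as a score), 16 become 15. Collinearity adds about 4-25% to the slope's standard error under the assumed gaps, most where the adjustment matters most. With few medial wearers the adjusted slope will be imprecise, which is why both versions should be shown.
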